### Participants

This study will be conducted at the Thomson Hospital, Kota Damansara, Malaysia. Thomson Hospital is a private tertiary-level health facility in Kota Damansara in Selangor, Malaysia. Participants will be invited to join this study by way of placing posters around the hospital’s primary care clinics and through social media. Hence, some of the volunteers recruited will include healthy hospital employees and their relatives, who became aware of the study through the posters placed in the hospital. Volunteers will also recruited using social media (Facebook, Instagram and WhatsApp).

### Study plan

Healthy subjects (n = 200-250) aged between 25 to 60 years old will be invited to participate in this study. At the time of screening, the purpose of the study and what the study entails will be explained to all volunteers who express an interest in joining the study. Before recruiting a subject for this study, a blood sample (12 mL) will be taken from all interested volunteers, where 10 mL of the blood will be sent to the Thomson Hospital medical diagnostic laboratory for various biochemical tests to establish baseline parameters to assist in the selection of healthy volunteers. The remaining 2 mL of blood will be used to quantify baseline plasma levels of vitamin E and anti-influenza antibodies. Then, 150 healthy volunteers who meet the inclusion and exclusion criteria (
Table 2) of this study, with the lowest level of anti-flu antibody and low plasma vitamin E, will be recruited for the study. Once a volunteer is selected for the study, a physician will explain the study protocol to the volunteer and ask the volunteer to provide a signed written informed consent to participate in this study.

**Table 2. T2:** Inclusion and exclusion criteria.

Inclusion criteria	Exclusion criteria
• 18–60 years-old • Healthy and free of diseases *(biochemical tests)*	• Have some health-related problems • On treatment or medication • Currently taking vitamin E supplements • Smoker • Received influenza A and B vaccination in the last 12 months • Obese (BMI > 35 kg/m ^2^) • Pregnant and/or breast-feeding

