## Objectives

This study aims to investigate the effects of different concentrations of TRF (400, 200, 100 or 50 mg) on the immune response to an influenza vaccine in healthy individuals and to elucidate the mechanism of action. Using high and low dosages is important to understand what may happen following TRF supplementation. This information can be used to develop this in a range of functionality. The specific objectives are (i) to compare antibody responses to influenza antigen following daily supplementation with TRF (400, 200, 100 or 50 mg) with placebo; (ii) to compare leucocyte profiles and cytokine levels in response to influenza antigen following daily supplementation with TRF (400, 200, 100 or 50 mg) with placebo; (iii) to identify differentially expressed plasma proteins following daily supplementation with TRF (400, 200, 100 or 50 mg) with placebo in the presence or absence of vaccination; and (iv) to correlate plasma vitamin E levels with antibody levels in volunteers with and without daily supplementation with TRF.

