### Outcomes

The primary outcomes of this trial will be comparing the antibody levels to influenza, the blood leucocyte profile, plasma vitamin E and cytokine production between the different groups. Secondary outcomes will be correlating plasma vitamin E levels with immune responses, plasma proteins and gene expression patterns.

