### Study approach

The study is expected to screen around 200–250 volunteers to recruit 150 volunteers required for this study. During the screening step, the volunteers will be subjected to a routine simple medical history and health screening to collect some data [age, gender, eating habits, occupation, lifestyle (smoking, alcohol, exercise), height, weight] as well as biochemical blood [full blood count (FBC), glucose, HBA1c, lipid profile, estimated glomerular filtration rate (EGFR), liver function tests (LFT)] and urine [full examination microscopy examination (FEME)] tests. Once the healthy volunteers are selected, they will be randomly assigned to one of the five study groups (
Table 1). The volunteers will be asked to attend three clinic sessions (days 0, 28 and 56) (
Figure 1). A trained phlebotomist will take blood via venepuncture, as shown in
Figure 1. After the blood-taking on day 0, the volunteers will be given a bottle containing sufficient test supplements for 28 days. The volunteers will be asked to take the supplement after dinner every day for 28 days.

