### Laboratory tests

*Antibodies to human influenza viruses*

The level of antibodies to influenza antigen in the plasma taken on days 0, 28 and 56 will be determined using an enzyme-linked immunosorbent assay (ELISA). Briefly, 100 μL of the flu vaccine (1 μg/mL) in coating buffer (Thermo Fischer Scientific, USA) will be added to 96-well ELISA plates (Corning C62-9018 plate) and incubated at 4°C for 24 hours. The plate will be washed thrice with 250 μL of ELISA wash buffer (Thermo Fischer Scientific, USA). Then, the plate will be blocked with 250 μL of ELISA diluent (Thermo Fischer Scientifc, USA) at room temperature for 2 hours. The plate will be washed thrice with 250 μL of ELISA wash buffer (Thermo Fischer Scientific, USA). The plate will be dried by gently tapping on absorbent paper. Then, 100 μL of diluted human serum (baseline, Day 28 and Day 56) will be added to each well in duplicates. A standard curve of anti-influenza A (Santa Cruz, USA) and anti-influenza B (Santa Cruz, USA) antibodies will be used to quantify anti-influenza A and anti-influenza B levels in the serum of healthy volunteers at different time points. Blank wells will contain 100 μL of ELISA diluent (Thermo Fischer Scientific, USA). After 2 hours at room temperature, the plate will be washed five times with 250 μL of ELISA wash buffer (Thermo Fischer Scientific, USA). Then, 100 μL of anti-human Ig (IgG, IgM and IgA) or anti-human IgG conjugated with horseradish peroxidase (HRP) (Abcam, USA) will be added to all wells. After one hour at room temperature, the plate will be washed five times with 250 μL of ELISA wash buffer (Thermo Fischer Scientific, USA), and 100 μL of TMB ELISA substrate (Abcam, UK) will be added to all wells. The enzymic reaction will be stopped after 10-20 mins by adding 100 μL Stop solution for TMB substrate (Abcam, UK). Absorbance at 450 nm will be read using a microplate reader (Tecan, Switzerland).

*Antigen-specific proliferation*

The buffy coat will be isolated from peripheral blood and cultured in the presence of the influenza vaccine for 72 hours. The antigen-specific proliferation will be measured using a commercial cell proliferation kit. The culture supernatant will be harvested and stored at -80°C until used for cytokine analysis.

*Plasma levels of vitamin E*

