Plasma levels of vitamin E will be quantified from samples taken on days 0, 28 and 56 using the high-performance liquid chromatography (HPLC) [Agilent HPLC 1200 with fluorescence detector, Agilent, USA] as desbribed previously.
^
36
^ Briefly, 1.0 mL of 0.9% sodium chloride (NaCl) will be added to 1.0 mL of human plasma in a glass test tube and vortexed for 30 seconds. Then, 1.0 mL ethanol-BHT (0.625 mg/mL) will be added, and the mixture will be vortexed for 30 seconds. Following this, 5.0 mL of n-hexane-BHT (0.05 mg/mL) will be added, and the mixture will be shaken overnight for 16 hours at 250 rpm, at 10°C using a shaking incubator (WIS-20, Witeg, Germany). After centrifugation (2500 rpm for 15 minutes at 4°C), the upper organic layer will be carefully extracted and transferred to a sterile tube. The tubes will be evaporated to dryness using a speed vacuum concentrator with CoolSafe -110°C cold trap (MaxiVac, LaboGene, Denmark). To obtain a standard curve for quantification, standard tocopherols (Toc) and tocotrienols (T3) (Hovid, Malaysia) will be separated on a Phenomenex KinetexTM PFP column (5.0 μm, 150 × 4.6 mm; Phenomenex) with a guard column using MeOH/H
_2_O (87:13) as an eluent at a flow rate of 0.9 mL/min. The dried samples will be reconstituted with 0.3 mL of mobile phase [methanol (MeOH) + butylated hydroxytoluene (BHT) (0.625 mg/mL)] and filtered using a nylon syringe fitted with a 0.45 μm, 4 mm filter (Chrominex, Singapore) prior to HPLC analysis. Then, 10 μL of the preparation will be injected into the HPLC (Agilent HPLC 1200, USA). The fluorescence detector will be set an excitation wavelength of 296 nm and emission wavelength of 325 nm and photomultiplier tube (PMT) gain will be set at 10.

*Cytokines*

Plasma and culture supernatant stored at -80°C will be thawed and used to quantify plasma levels of cytokines [e.g. interferon-gamma (IFN-γ) (MABtech, USA), tumour necrosis factor-alpha (TNFα) (MABtech, USA), interleukin-12 (IL-12) (MABtech, USA), and interleukin-17A (IL-17A) (MABtech, USA)] using commercial ELISA kits.

*Protein expression*

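### Enrolment selects on the same two markers, antibody and vitamin E, that objective (iv) correlates, so the raw correlation can be distorted, mainly at Day 0 and in the placebo arm

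*Protocol article*

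**What the plan says.** All references are to the protocol article.

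- **Selection (Study plan).** A screening sample is assayed for both markers: "The remaining 2 mL of blood will be used to quantify baseline plasma levels of vitamin E and anti-influenza antibodies". From those who meet the Table 2 criteria, 150 volunteers "with the lowest level of anti-flu antibody and low plasma vitamin E, will be recruited for the study". No cut-off is given for either marker, and no rule for combining them.
- **Numbers (Study approach).** "The study is expected to screen around 200–250 volunteers to recruit 150 volunteers required for this study". Allocation to the five arms follows selection.
- **Use of the markers (Objectives, Outcomes).** Objective (iv) is "to correlate plasma vitamin E levels with antibody levels in volunteers with and without daily supplementation with TRF". The Outcomes section adds: "Secondary outcomes will be correlating plasma vitamin E levels with immune responses, plasma proteins and gene expression patterns". Neither place says which visit is used, or whether levels or changes are correlated.
- **Measurement (Laboratory tests).** Both markers are measured at all three visits: "The level of antibodies to influenza antigen in the plasma taken on days 0, 28 and 56 will be determined" and "Plasma levels of vitamin E will be quantified from samples taken on days 0, 28 and 56".

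**The concern.** When people are admitted to a sample because of their values on two variables, the correlation of those variables in the sample need not match the one in the group they came from. There are two mechanisms. Truncating each variable separately narrows both ranges and weakens a real correlation. Ranking on a combination of the two lets a high value on one be offset by a low value on the other, which pushes the correlation in a negative direction even where none exists.

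The exposed part is the unsupplemented side of objective (iv): Day 0 values, and the placebo arm at later visits, where no dose spreads vitamin E. A real positive link between vitamin E and antibody could look weak or absent there, or under a combined ranking even negative, partly because of how volunteers were chosen.

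**Working it through.** The protocol gives no figure for the correlation, so there is none to reproduce. What follows measures how far selection can move it.

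**Inputs from the protocol.** 150 enrolled of 200–250 screened: 150/200 = 75% and 150/250 = 60% kept.

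**Assumptions (not in the protocol).** Antibody *A* and vitamin E *V* are standard bivariate normal at screening. The unselected correlation is 0 or 0.30. Persistence from screening to Day 56 is 0.6 for antibody and 0.8 for vitamin E. Day 0 figures treat the screening value as the Day 0 value.

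**1. Combined ranking, true correlation 0, Day 0.** Keep the lowest fraction *p* of *S* = *A* + *V*. The variance of *A* − *V* stays at 2, and the variance of *S* falls to 2*v*, with *v* = 1 − *z*λ − λ², *z* = Φ⁻¹(*p*), λ = φ(*z*)/*p*. Then *r* = (*v* − 1)/(*v* + 1).

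- *p* = 0.75: *z* = 0.674, λ = 0.424, *v* = 0.535, *r* = −0.465/1.535 = −0.30.
- *p* = 0.60: *z* = 0.253, λ = 0.644, *v* = 0.422, *r* = −0.578/1.422 = −0.41.

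**2. Same rule, Day 56, no supplementation.** The covariance becomes 0.6 × 0.8 × (*v* − 1)/2. The variances become 0.36(*v* + 1)/2 + 0.64 for antibody and 0.64(*v* + 1)/2 + 0.36 for vitamin E.

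- *p* = 0.75: −0.112/√(0.916 × 0.851) = −0.13.
- *p* = 0.60: −0.139/√(0.896 × 0.815) = −0.16.

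**3. Day 0 under different rules** (simulation of bivariate normal pairs, 75% / 60% kept).

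| Rule | True 0 | True 0.30 |
|---|---|---|
| Separate cut-offs on both | 0.00 / 0.00 | 0.21 / 0.18 |
| Combined ranking | −0.30 / −0.41 | 0.00 / −0.12 |
| Antibody only | 0.00 / 0.00 | 0.22 / 0.20 |

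**4. Fewer eligible volunteers.** Selection on the markers acts only on those who pass Table 2, so the true fraction kept is higher than 60–75%. Combined ranking, true 0:

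- 180 eligible (*p* = 0.83, *v* = 0.620): −0.380/1.620 = −0.23 at Day 0.
- 160 eligible (*p* = 0.94, *v* = 0.782): −0.218/1.782 = −0.12 at Day 0; −0.052/√(0.961 × 0.930), about −0.05, at Day 56.

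**5. Follow-up with a real link** (no baseline correlation; ranges run over weak to strong persistence and 75% to 60% kept). In the placebo arm a true 0.29 becomes 0.27–0.28 under separate cut-offs, and between 0.25 and 0.10 under a combined ranking. With all arms pooled and vitamin E raised by dose, a true 0.35 becomes 0.34–0.35 and between 0.32 and 0.22 respectively.

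**6. Contrast of supplemented with unsupplemented volunteers.** A uniform rise in vitamin E leaves the within-arm correlation unchanged, so the shift cancels. If the rise varies between people (assumed variance 1, added to the vitamin E variance in step 2), the supplemented arm has −0.112/√(0.916 × 1.851) = −0.09 against −0.13 at 75%, and −0.139/√(0.896 × 1.815) = −0.11 against −0.16 at 60%. The arms differ by about 0.04 to 0.05.

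**7. Does conditioning remove it?** Under the linear normal model, selection depends only on the screening values (beyond Table 2), so the follow-up association given those values is the same before and after selection. In simulation the partial correlation did not change under either rule.

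**The case against.** The strongest case against runs as follows.

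- **The rule is not stated.** The wording asks for the lowest antibody but only for low vitamin E. That reads at least as naturally as a ranking on antibody with a vitamin E threshold as it does a combined score. Without a combined score no correlation is created. This stands.
- **The largest figures are for Day 0, which objective (iv) does not name.** Study approach also describes a Day 0 draw after selection. If that is a new sample with persistence of 0.8 for both markers, the −0.30 and −0.41 fall to about −0.17 and −0.23. This stands, but objective (iv) names no other visit either, and it expressly includes volunteers without supplementation.
- **Selection may be mild.** Step 4 bears this out.
- **The Day 56 shift is small against noise.** The standard error of a placebo-arm correlation is about 1/√27 = 0.19 with 30 volunteers and 1/√23 = 0.21 with 26. This limits the practical harm, but the shift is systematic and the remedy costs little.
- **Enrichment is deliberate.** The protocol does not claim a correlation for unselected people. Agreed, and the choice to enrich is not criticised here.

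A reader might go further and infer that recruitment manufactures a negative correlation, or that a difference between supplemented and unsupplemented volunteers would be an artefact of selection. The document supports neither. The first needs a rule it does not contain. The second fails because allocation follows selection, so every arm inherits the same distortion and most of it cancels (step 6).

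**Conclusion.** The concern holds in conditional form: the raw correlation can be distorted, and the protocol does not allow anyone to say by how much. With 60–75% kept, the Day 0 effect runs from attenuation only (0.30 to about 0.2) under separate cut-offs to a spurious −0.3 to −0.4 under a combined ranking. At Day 56 without supplementation and with no true correlation, it runs from nil to about −0.13 to −0.16, and less if few eligible volunteers are turned away. These figures rest on normality, on the assumed unselected correlations and on the assumed persistence of 0.6 and 0.8, none of which the protocol gives.

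One secondary, associational outcome is affected. The randomised comparisons of antibody, leucocytes and cytokines keep their validity. It remains worth acting on, because both screening values are already collected and conditioning on them deals with the problem whichever rule was used.

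**What to change.** 1. Run the Day 28 and Day 56 correlations of objective (iv) within arm, as partial correlations or regressions conditional on screening antibody and screening vitamin E.
2. State that any raw Day 0 or placebo-arm correlation applies only to the selected low-antibody, low-vitamin-E population.
3. Where consent permits, also report the pre-vaccination correlation in all screened volunteers, as a supplement. It describes antibody before vaccination, so it cannot replace the follow-up analysis. Study plan places written consent after selection, and Study status says that screening is under way, so permission to use data from volunteers not enrolled has to be checked first.

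**Cost.** A change of analysis wording, with no new blood or assays. Two degrees of freedom per arm: with 26 completers the approximate standard error goes from 1/√23 = 0.21 to 1/√21 = 0.22. The result is an association conditional on baseline, not a raw one, and must be described as such.

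Changing the selection rule is not recommended. It would alter recruitment in progress, and selecting on antibody alone gives 0.22 / 0.20 for a true 0.30, against 0.21 / 0.18 with separate cut-offs.

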## Protocol

### Ethics consideration

The Monash University Human Ethics Committee (MUHREC) have reviewed and approved the study protocol [MUHREC 30401] (27 January 2022). In addition, the study will be conducted in accordance with the principles of the Declaration of Helsinki 2013 and the Malaysian laws on medical research involving human subjects. All changes to changes to the protocol will require approval from MUHREC before they are applied. All data, including personal information about potential and enrolled participants for this study, will be stored in a file kept in a locked cabinet in a locked room in Monash facilities. The digital data will be stored on a secure shared drive behind the Monash firewall. Only the chief investigator will have access to these files. Upon completion of the study, all data will be stored and handled by Monash University Malaysia for at least 15 years after the study has ended. Only researchers listed in the ethics approval will have access to the research data.

This protocol has been registered with the Australian New Zealand Clinical Trials Registry (ANZCTR) [
ACTRN12622000844741] on 15 June 2022.

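### The only signed consent the protocol describes comes after the screening blood draw, the study assays and selection

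*Protocol article*

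**What the plan says.** The Study plan section of the protocol article sets out the order of events:

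- At screening, interested volunteers are told the study's purpose and what it involves.
- Blood is then drawn: "Before recruiting a subject for this study, a blood sample (12 mL) will be taken from all interested volunteers". Of the 12 mL, 10 mL goes to the hospital laboratory for biochemical tests. For the rest, "The remaining 2 mL of blood will be used to quantify baseline plasma levels of vitamin E and anti-influenza antibodies".
- From those who meet the eligibility criteria, 150 people "with the lowest level of anti-flu antibody and low plasma vitamin E, will be recruited for the study".
- Consent follows: "Once a volunteer is selected for the study, a physician will explain the study protocol to the volunteer", and at that step will "ask the volunteer to provide a signed written informed consent to participate in this study".

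The Study approach section adds a medical history, lifestyle and demographic data, and a urine test to the screening step. It gives the scale: "The study is expected to screen around 200–250 volunteers to recruit 150 volunteers required for this study".

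The Ethics consideration section covers storage of personal information on potential as well as enrolled participants, and keeps all data for at least 15 years. It also records ethics committee approval and requires the committee to approve any change. The Study status section says that volunteers are now being screened.

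**The concern.** The trial treats a signed consent as necessary, yet its text schedules that signature after the first invasive procedure done for the trial. The screening draw is not ordinary care. It is taken to choose participants, and 2 mL of it is for two assays whose results help decide who enters.

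The people most affected are those who are not chosen. They give blood, urine and personal health data, and the described process then ends for them before anyone asks for a signature. Their information still falls within the planned data storage. A site that works from this text would hold identifiable screening data with no documented consent from those volunteers. A blood draw already made cannot be undone by a later signature.

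**Working it through.** No sample-size or error-rate calculation applies. The check has two parts: the order of steps, and a count of the people affected.

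**Order of steps.** The Study plan section uses explicit time markers. The draw comes before recruitment, selection comes next, and the physician's explanation with the signature is triggered once a person has been selected. Selection also cannot come before the draw, because it uses the antibody and vitamin E results from that blood. The sequence is therefore:

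1. explanation to all interested volunteers (no signature mentioned);
2. 12 mL draw from all of them, with history, lifestyle data and urine test in the same screening stage (Study approach section);
3. assays and biochemical tests;
4. selection of 150;
5. physician's explanation and signed consent.

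No other written consent step is described anywhere in the document.

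**Inputs for the count.**

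- Screened: around 200–250 (Study approach section).
- Recruited: 150 (Study plan, Study approach and Sample size sections; Table 1).
- Blood at screening: 12 mL per person (Study plan section).

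**The plan's own figure.** Table 1 has 5 arms × 30 = 150, which agrees with the text. The blood volume also adds up: 10 mL + 2 mL = 12 mL.

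**People who do not reach the signing step** = screened − recruited.

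- Lower end: 200 − 150 = 50, and 50 / 200 = 25%.
- Upper end: 250 − 150 = 100, and 100 / 250 = 40%.

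**People who undergo screening procedures before the described signature:** all of those screened, around 200–250. For the 150 who enrol, the signature comes later, at selection. For the other 50–100, the text describes none.

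**Effect of moving the signature ahead of the draw.** Written consents rise from 150 to 200–250, that is by 50–100. The 30 per arm and the analysis stay as they are.

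**The case against.** The strongest reply is that the article does not say that nothing is signed at screening. The signature it describes is for taking part in the trial. A separate screening consent could sit in the full protocol, or among the consent pages removed from the text under review. This stands in part. A reader might infer that 200–250 people are bled with no written consent at all, or that 50–100 never sign anything; the document does not establish either. It does place the only signature it describes after the draw, the assays and selection. That is a stated sequence and not a detail lost in condensing. If a screening consent exists, this section is misleading and still needs correcting.

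Second, volunteers are told about the study before the draw and come forward by choice. That is right. They are not uninformed, and the text does not say that the explanation is only oral. The gap is in documented consent.

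Third, the ethics committee approved the protocol, and the article states that "the study will be conducted in accordance with the principles of the Declaration of Helsinki 2013". A reader might infer a direct breach of that commitment. The document quotes no clause on the timing or form of consent, so this conflict cannot be shown from it, and the point does not need it. Equally, approval does not change the order that the text sets out.

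Two further inferences should not be drawn. Nothing in the document shows that data from unselected volunteers could not be used or reported at all; the supportable statement is that no documented consent is described for them. And although some volunteers are hospital employees or their relatives, and samples go to that hospital's laboratory, this is a separate matter that reordering consent would not change.

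**Conclusion.** The point holds as a defect in the stated order of procedures. As written, around 200–250 volunteers receive an explanation but have blood, urine, history and lifestyle data collected before any described signed consent. Roughly 50–100 of them (25–40%) are not selected and do not reach the signing step, while storage of data on potential participants is planned.

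The count assumes that the screening range in the Study approach section is met and that exactly 150 enrol. The Study plan section gives the same 200–250 as the number invited, so the figures are approximate and would be lower if fewer attended. The finding also assumes that the text describes actual practice; a screening consent that is already in use would reduce it to a correction of wording.

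It is a matter of participant protection. It has no bearing on power, type I error, bias or the analysis.

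**What to change.** Reorder the Study plan section so that the explanation and a signed consent come before the screening blood draw, urine test and history. Either the full trial consent or a separate screening consent would serve. It should cover:

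- the screening procedures themselves;
- use of the antibody and vitamin E results for selection;
- retention of data from people who are not selected.

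If a screening consent is already in use, amend the section to say so and to say when it is signed.

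Because screening is under way, reordering does nothing for volunteers who have already been bled. The amendment should go to the ethics committee with a plan for them, including those already found ineligible or not selected.

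The cost is a protocol and consent-form amendment, about 50–100 more signatures, and whatever contact with already-screened volunteers the committee requires. The sample size does not change.
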